#### Methods of randomization and allocation concealment

Block randomization with a random block size of 4 to 6 will be used to randomize eligible participants equally into the two groups. A computer-generated list of numbers known only to an independent administrator will be used in the randomization process. The group allocation will be enclosed in sequentially numbered opaque sealed envelopes. After the participants have finished all baseline assessments and the blinded assessor has confirmed their eligibility, then the independent administrator will give the participants a sealed envelope. The participants will then open the envelope to reveal their group allocation. The research assistant who is responsible for phone-call follow-up will then look at their opened envelopes to log the participants' code and allocation.

#### Methods of blinding

The researchers who perform the assessment and analysis will be blinded to group allocation.

### Assessment of compliance

Participants' attendance at the training course will be recorded. To assess the compliance with home practice of self-administered acupressure, participants will be given an **acupressure logbook** to record their daily practice, including frequency and time spent on practicing self-administered acupressure during the 12-week study period. Similarly, participants in the control group will receive a **knee health logbook** to record their daily compliance to each instruction by yes/no questions. The same follow-up procedure will be conducted to assess their compliance.

### Assessment of acceptability and feedbacks

The investigator-designed Evaluation Questionnaire was administered to both groups to evaluate the participants' feedback on the training course. The questionnaire includes a 10-point single item-scale (ranging from 1 to 10) to assess the participants' acceptability of self-administered acupressure or knee health education. Open-end questions will also be included to collect qualitative feedback regarding the best parts of the training and suggestions for any improvement.

### Assessment of safety

#### i. Reasons for withdrawal

When a subject withdraws before completing the study, the reasons for withdrawal will be recorded.

#### ii. Adverse events

The instructor will ask, using open-ended questions, whether the participants experienced any adverse events during the assessment visit for immediate action and follow-up. The severity and relationship of the adverse event to the intervention will be investigated and documented.

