### Study design

Participants will attend two weekly 2-hour of self-administered acupressure training or knee health education according to the group allocation in a classroom at the School Nursing, the Hong Kong Polytechnic University. The participants will be trained to perform self-administered acupressure by an acupuncturist or receive knee health education by a registered nurse. To enhance interaction and ensure the quality of teaching, each class will be conducted in a small group of 4 to 6 subjects.

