#### Fidelity of self-administered acupressure training by instructors

All the training materials will be reviewed and approved by the research team. A registered Chinese medicine practitioner with at least 5 years' clinical experience and at least a Master's degree will be recruited as an instructor to teach self-administered acupressure. The PA who is a senior acupuncturist, will go through the training materials with the instructor to ensure he/she understands the content and any pertinent details specific to the protocol. The instructor will run a demonstration course so that the PA and Co-A can assess whether the course content is being conveyed properly. PA will visit the first four classes and then randomly visit (at least one per month) to ensure the training content is adherence to the research protocol.

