#### Fidelity of self-administered acupressure in participants

The capability of participants for self-administered acupressure will be inspected by the instructor with a **competency checklist** in each session. The practice of self-administered acupressure will be assessed in four domains: accuracy of locating acupoints, acupressure technique, strength, and frequency of acupressure at each acupoint. Advice and correction will be made when necessary. Video on steps of locating acupoints and instruction on the technique of acupressure will be sent to the participants via WhatsApp for their reference at home. A contact phone number will be available for participants to contact the research assistant if they have any queries regarding the acupressure. Participants' acupressure technique will be assessed again at week 4.

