#### Monitoring of compliance at home (Control group)

Similar to the self-administered acupressure group, telephone follow-up will be conducted by the instructor to remind them to follow the instruction and answer queries regarding the education content during the first week; reminders will be made twice a week via WhatsApp by the research assistant during the remaining study period to remind subjects to follow the instruction. Participants will record whether they have followed the knee health instructions in a logbook.

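### Adverse events are elicited by the instructor, who by inference differs between arms and is unblinded, so harms ascertainment can differ by arm by design and does not fit the unqualified blinding statement

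*Protocol*

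**What the plan says.** Under Assessment of safety, the adverse events paragraph of the protocol states: "The instructor will ask, using open-ended questions, whether the participants experienced any adverse events during the assessment visit". It gives the purpose as prompt action and follow-up, and adds: "The severity and relationship of the adverse event to the intervention will be investigated and documented". It does not say who makes that judgement.

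The instructor is not one person across the trial. Study design says that participants will be "trained to perform self-administered acupressure by an acupuncturist or receive knee health education by a registered nurse". The section on instructor fidelity adds that a registered Chinese medicine practitioner "will be recruited as an instructor to teach self-administered acupressure". The control arm's teacher is also called the instructor; for that arm, "telephone follow-up will be conducted by the instructor to remind them to follow the instruction".

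Methods of blinding states: "The researchers who perform the assessment and analysis will be blinded to group allocation". It makes no exception for safety.

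The section on participant fidelity says: "Participants' acupressure technique will be assessed again at week 4". It does not say who does this or whether it takes place at the outcome visit. Week 4 is one of the outcome assessment weeks.

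Table 1 schedules adverse event monitoring at weeks 1, 2, 4, 8 and 12, without distinction by arm.

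**The concern.** An open-ended question about harms finds what the participant chooses to mention and what the questioner follows up. Both depend on who asks. Here the questioner in one arm is the practitioner who taught the acupressure, and in the other a nurse who taught the education course. Each knows the allocation and has a teaching relationship with the participant. A between-arm difference in reported events, or the absence of one, could then reflect the questioner and not the intervention. The direction cannot be predicted: a participant may be reluctant to complain to the teacher, and a practitioner who expects soreness from pressing may either probe for it or dismiss it as normal.

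The harms data matter here. Section 8 of the protocol expects slight discomfort when pressure is applied, and section 6 foresees recommending the method to healthcare providers if it works. A reader of the results will compare harms by arm whether or not a test is planned. The judgement of severity and relatedness is exposed in the same way, since no blinded person is named for it.

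**Working it through.** **Step 1. Who asks, set against who is blinded.**

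| Question | What the protocol gives | Where |
|---|---|---|
| Who elicits harms? | The instructor, by open-ended question, at the assessment visit | Adverse events |
| Who is that in the acupressure arm? | An acupuncturist; a Chinese medicine practitioner recruited to teach that arm | Study design; fidelity of training by instructors |
| Who is that in the education arm? | A registered nurse | Study design |
| Do they know the allocation? | Necessarily: they teach and telephone that arm's participants | Treatment protocol; compliance monitoring, both arms |
| Who is blinded? | Those who perform assessment and analysis, with no exception stated | Methods of blinding |
| Who judges severity and relatedness? | Not stated | Adverse events |

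The protocol nowhere says in terms that each arm's own instructor asks that arm's participants. This is an inference, but a strong one, because no instructor common to both arms is described. On any reading the questioner is unblinded.

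**Step 2. Plan figures.** The protocol states no adverse event rate and no detection rate, so there is no safety figure to reproduce. The only figure used below is the number per arm: 314 / 2 = 157. This agrees with the sample size section: 133 / 0.85 = 156.5, rounded up to 157.

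**Step 3. Illustration with assumed rates.** Let the true event proportion be t in both arms, and let the two instructors detect shares a and b of events. The observed proportions are t·a and t·b, so the observed risk ratio is a / b whatever t is.

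- a = 0.90, b = 0.80: 0.90 / 0.80 = 1.125, about 1.1.
- a = 0.90, b = 0.60: 0.90 / 0.60 = 1.5.

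In participants, with t = 0.10 and 157 per arm:

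- 157 × 0.10 × (0.90 − 0.80) = 1.6 fewer found in the second arm.
- 157 × 0.10 × (0.90 − 0.60) = 4.7 fewer.

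**Step 4. Chance of a falsely significant difference.** The normal approximation for two proportions, with two-sided 5% significance, gives the probability of a significant result in favour of the arm with less detection as Φ((d − 1.96·se₀) / se₁). Here d = t·(a − b), se₀ is the pooled standard error and se₁ the unpooled one. With no bias this probability is 2.5%.

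| Assumed true rate t | 90% vs 80% detected | 90% vs 60% detected |
|---|---|---|
| 5% | 4.1% | 10.4% |
| 10% | 5.0% | 17.0% |
| 20% | 6.8% | 31.8% |
| 30% | 8.8% | 48.0% |

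A modest detection gap does little at low event rates. A wide gap matters once events are common. The approximation is rough in the 5% row, where fewer than ten events per arm are expected.

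**The case against.** The strongest case on the other side has four parts.

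First, the question is there for participant care. Its stated purpose is prompt action and follow-up, the analysis section plans no between-arm test of adverse events, and participants have other channels: calls, WhatsApp contact and a research assistant whom they can ring. This stands as a limit on importance. It does not remove the problem, because the events recorded this way are the trial's harms data and will be read by arm.

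Second, the method and schedule are worded identically for both arms. That is true, but the same open-ended question put by two different unblinded people is not the same measurement.

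Third, section 8 expects adverse events to be minimal and reports no significant side effects in the pilot. At low rates a modest detection gap changes little, as the first rows of the table show.

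Fourth, using someone other than the outcome assessor for adverse events protects that assessor, since a participant who describes discomfort from pressing reveals the arm. This stands, and it rules out handing the question to the blinded assessor: even if asked last, it could unblind that person for weeks 8 and 12.

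A reader might go further and infer that blinding of the efficacy assessor is undermined, because an arm-identifying instructor is at the visit and technique is re-checked in one arm at week 4. The protocol does not support this. The randomization section names a separate blinded assessor, and nowhere is the instructor given the NRS, WOMAC, SF-6D, TUG or gait speed. The week-4 check has no named examiner and is not placed at the outcome visit. The order of contacts and the handling of logbooks are operational detail that the protocol leaves open, not something it states wrongly.

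**Conclusion.** The point holds for safety. Harms are elicited by an unblinded instructor who, by strong inference from the sections on study design, instructor fidelity and compliance monitoring, differs in profession between arms. Ascertainment can therefore differ by arm by design, and the adverse events paragraph does not fit the blanket statement under Methods of blinding.

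The size is unknown. The risk ratios of about 1.1 and 1.5, and the chances of a falsely significant difference (4–9% and 10–48% for assumed true rates of 5% to 30%), rest on assumed detection rates, equal true rates and 157 participants per arm. They show what such a gap could do, not what it will do. The direction is not predictable either.

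No conclusion follows for the primary outcome or for the assessor-timed tests. For these the protocol describes a separate blinded assessor, and the week-4 check is a matter to clarify, not a demonstrated breach.

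**What to change.** - **Adverse events paragraph.** Have one common role ask the same scripted question in both arms, after the outcome measures for that visit are recorded. That role should be neither the arm's instructor nor the blinded outcome assessor. The research assistant who logs allocation and sends the reminders to both arms is an obvious candidate, provided that this is not the person doing the blinded assessment. Keep the instructors for follow-up of events already reported.
- **Methods of blinding.** State that assessor blinding covers the efficacy outcomes, so that the two sections agree.
- **Week-4 technique check.** Name who does it, and keep it away from the blinded assessor.

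**Cost.** A few sentences of amendment, one short script and a small shift of tasks among existing staff. The person asking remains unblinded, so the change removes the difference in questioner between arms but not knowledge of allocation. No change to sample size or to the primary analysis is needed.

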## **8. Potential hazards to participants**

Since both self-administered acupressure and knee health education are non-invasive, the problem of adverse event will be minimal. The treatments used in the protocol have been tested in the pilot study and no participant had reported significant side effects. It is likely that the subjects experience slight discomfort when they are requested to apply pressure on the acupoints. Such a phenomenon will be explained

to the subjects in advance and the pressure will only be applied for a short period of time, which would obviously not produce any injury to the subjects. We will have phone calls and Whatsapp reminders (twice per week) and the subjects can raise questions if they have encountered any discomfort. The subjects can also call our Research Assistant at any time to have our assistance.

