| Fast Gait Speed                                                 |           | √        |                              |   | √                         | √ | √  |
| Medication Use                                                  |           | √        |                              |   | √                         | √ | √  |
| Others                                                   |           |          |                              |   |                           |   |    |
| Acupressure/ health instruction logbook                         |           |          | √                            | √ | √                         | √ | √  |
| Adverse event monitoring                                        |           |          | √                            | √ | √                         | √ | √  |

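### The only active question about adverse events is open-ended and nothing asks directly about the acupoint discomfort the protocol expects, so local reactions may be under-reported, mainly in the acupressure arm.

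*Protocol*

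**What the plan says.** Four places in the protocol bear on this.

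- **Assessment of safety, ii. Adverse events.** The method of asking is fixed: "The instructor will ask, using open-ended questions, whether the participants experienced any adverse events during the assessment visit". For each event, "The severity and relationship of the adverse event to the intervention will be investigated and documented". No list of symptoms or local reactions is given.
- **Section 8, Potential hazards to participants.** A local effect of the intervention is foreseen: "It is likely that the subjects experience slight discomfort when they are requested to apply pressure on the acupoints". On informing participants, the text says "Such a phenomenon will be explained" to them beforehand. It then gives a reassurance: "the pressure will only be applied for a short period of time, which would obviously not produce any injury to the subjects".
- **Section 8, contact routes.** Alongside phone calls and twice-weekly WhatsApp reminders, "the subjects can raise questions if they have encountered any discomfort". In addition, "The subjects can also call our Research Assistant at any time to have our assistance".
- **Table 1.** The row "Adverse event monitoring" is ticked at weeks 1, 2, 4, 8 and 12.

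**The concern.** Discomfort at the pressed points is the one effect of acupressure that the investigators predict. Participants hear about it before they start. Whether it is counted then depends on whether each of them, asked an open question, regards it as an adverse event. Someone who has been told to expect it may not mention it.

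The advance explanation is about pressing acupoints, so it is relevant to one arm. If it discourages reporting, the loss would fall mainly on the acupressure arm, and the comparison of harms between arms would look more favourable to acupressure than it should.

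This matters because section 6 (Purpose and Potential) would use a positive result to recommend home acupressure to people with knee osteoarthritis in the community. Such a recommendation needs a usable account of tolerability. How events are asked about is a matter of data collection, and a later analysis plan cannot recover events that nobody elicited.

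**Working it through.** The protocol states no figure on this point, so there is none to reproduce. The check is whether any other planned route asks about local reactions, or carries them into the adverse-event record.

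| Route | Where in the protocol | Asks about local reactions? | Linked to the adverse-event record? |
|---|---|---|---|
| Open-ended question by the instructor | Assessment of safety, ii | Only if the participant thinks of them | Yes |
| Scheduled monitoring, weeks 1, 2, 4, 8, 12 | Table 1 | States when, not how | Yes |
| Phone calls and WhatsApp reminders | Treatment protocol; Monitoring of compliance; section 8 | No; for reminders and queries, and the participant must raise discomfort | Not stated |
| Call to the research assistant | Section 8 | No; the participant must call | Not stated |
| Discussion of home practice in session 2 | Treatment protocol | Covers issues participants raise | Not stated |
| Logbooks | Monitoring of compliance; Assessment of compliance; Medication Use | No; practice, adherence and analgesic use | Not stated |
| Reasons for withdrawal | Assessment of safety, i | Only if a reaction leads to withdrawal | Not stated |
| NRS and WOMAC, weeks 4, 8, 12 | Section 4; Table 1 | Knee pain in both arms, but not attributed to practice; no bruising or skin change | No |

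Three steps follow.

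1. Staff start several of these contacts, but in none of them is a question about soreness, bruising or skin change planned. Asking the open question five times does not make it a targeted one.
2. Discomfort raised outside the open question has no stated path into the adverse-event record.
3. The number reported in the acupressure arm can be written as 157 × p × c. Here 157 = 314 / 2 is the number randomized to that arm, p is the true proportion with a local reaction, and c is the share of those that the open question finds. The control arm has its own p and c. The comparison is distorted if c is lower in the acupressure arm. The protocol gives neither p nor c for either arm, so a difference in c is plausible but its size cannot be calculated.

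**The case against.** Open-ended questioning is a legitimate method, and the protocol also requires severity and relationship to be documented. Slight discomfort while pressing can be seen as a sensation of the procedure, and counting it as an adverse event is a choice. Exact prompts are often left to the case report form. Harms are not among the specific aims in section 2, and no effectiveness analysis depends on them. Worsening knee pain is in large part already measured by NRS and WOMAC in both arms, with analgesic use logged throughout. All of this stands, and it keeps the priority low. It does not remove the gap, because the protocol does fix the method of asking and leaves the one predicted effect without a direct question.

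A reader might also infer more than the text supports:

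- **That participants are told discomfort is normal.** The protocol says only that it will be explained.
- **That the harm rate in the acupressure arm is biased downward.** The documents do not show this. Explaining discomfort and inviting participants to raise it could also prompt reports.
- **That there is no other channel.** There are several, as tabulated above. They are untargeted and have no stated link to the adverse-event record.
- **That the pilot bounds the risk.** Zero events among the 17 pilot acupressure participants would give a one-sided 95% upper limit of 1 − 0.05^(1/17) = 16.2%. But the pilot remark in section 8 concerns significant side effects, so this limit says nothing about soreness or bruising. Nor does the no-injury sentence rest on the pilot: the text ties it to the short time for which pressure is applied.
- **That this trial would be the only sizeable source of harm data.** The reference list cites systematic reviews of acupressure and a self-acupressure trial in knee osteoarthritis. Their harm data cannot be seen from here.

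**Conclusion.** The point holds in a limited form. The only active elicitation described is an open-ended question. The local effect that the protocol calls likely is explained beforehand, no targeted question is planned, and the informal routes are not tied to adverse-event recording. Expected local reactions may therefore be under-reported, mainly in the acupressure arm.

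This rests on one assumption: that some participants will not volunteer an effect they were told to expect. The size of any under-count cannot be derived from the documents, and no estimate is offered. The primary result is untouched; what weakens is the trial's ability to describe local tolerability. Priority: low.

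**What to change.** 1. Keep the open-ended question, and ask it first.
2. At the adverse-event contacts already in Table 1, add a short identical set of yes/no items worded so that they apply in both arms: new soreness or tenderness around the knee; bruising or skin change around the knee; worse knee pain after practice or after following the instructions.
3. State that discomfort raised by phone or WhatsApp is entered in the adverse-event record, in both arms.
4. Report the solicited items by arm, in a table separate from the open-ended events.
5. Optionally, delete the word *obviously* from the no-injury sentence in section 8.

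The cost is a few tick-boxes on an existing form, one rule for staff and one descriptive table, with no extra visit. The downside is that solicited rates run higher than volunteered ones, and participants know their allocation. The two kinds of report must therefore not be pooled, and the solicited items should be read with that in mind.
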